### Data collection

We will develop a series of data collection tools for use in each intervention and control area and keep detailed records of what data is collected and how it is obtained. Data collection will be completed in the 20 intervention areas via sourcing and analysis of relevant documentation by email; an initial site visit, and structured telephone interviews with public health and licensing practitioners. Drawing on the research team’s (which includes practitioner advisors with expertise in public health and licensing) knowledge, we have drawn up an initial list of documents to request. The document request will be made by email prior to each site visit so that fieldworkers can extract relevant data from the documents to populate a series of timelines. These timelines will describe different types of activities relevant to PHT engagement in licensing at six monthly intervals over the study period. The timelines will form the dataset upon which we will apply our measure of intensity of activity. The initial list of activities that data collection will focus on is provided in Table 5 below.

**Table 5 Tab5:** List of local Public Health and Licensing activities that data will be collected on

Intervention Components (Indicators)	Licensing activity/regime
a. A systematic process for review of new licensing applications & variations (known point of contact, clear criteria, use of routine data) b. Active response to applications (liaison with responsible authorities, licensing reps, applicants; representations) c. Development of bespoke datasets (robust/ systematised local data collection on harms etc.) d. Engagement with licensing authorities (meetings, awareness raising, licensing policy input) e. Activity towards development of cumulative impact/overprovision areas (submissions, representations, consultation) f. Public health-led activity to involve the public/local communities (depth, breadth of involvement, activity of local licensing fora) g. Public health-led engagement with licensees (‘Reducing the Strength’ schemes; advertising/ promotion bans) h. Any other public health led activity to influence licensing/licensees.	i. Licence application levels, types, conditions j. Licence decisions k. Cumulative impact/overprovision policies/areas l. Outlet density by type. m. Late night levies n. Health commitment in licensing policies o. Reducing the strength scheme sign up p. Local advertising/promotion ban q. Health as a licensing objective (if introduced locally in England) r. Any other relevant elements

Most of these indicators and interim licensing outcomes leave a documentary trail (e.g. databases, policy statements, records of meetings) which we will identify with assistance from local contacts and supplement with further information obtained from interviews. The list will be further developed following the initial scoping calls with potential intervention areas and consultation with the study advisory group, informed by prior research. The development process will also be informed by discussion with the lead authors of studies which developed three other alcohol policy measures in the literature [72–74].

The intervention area site visits will provide fieldworkers with the opportunity to interview alcohol leads from the local PHTs and to meet licensing representatives. The main purpose will be to fact-check and add to the various activity timelines produced from the document analysis, and to request further documents if necessary. Besides interviewing current alcohol leads, fieldworkers will (if necessary) seek interviews with previous leads to ensure data collection covers the whole study period. The availability of interviewees with knowledge of the whole study period will be one of the criteria considered when selecting participating areas. The data collection will be completed by sourcing relevant documentation by email and via further structured telephone interviews as needed. Data collection in control areas will involve similar documentation analysis and structured telephone interviews. It is anticipated that the type and quantity of documentation will vary greatly by area, as some intervention areas will have engaged in more relevant activities than others, whilst control areas will be selected because of their lack of engagement.

We will also collect data on potential confounding activities in each area such as: local initiatives around alcohol screening/brief advice; public information & education initiatives; police-led initiatives in the night-time economy; drink driving initiatives; industry-led best practice schemes; or any other major relevant confounding activity. Whilst we will aim to map confounding activities on our timeline we anticipate that some confounders are likely to be specific to particular area contexts and knowledge of them will emerge during the course of our fieldwork. We will incorporate analysis of wider confounding factors into our overall analysis and ensure that it is taken into account of when interpreting our findings, in particular how PHT activity in the licensing arena is positioned within the wider system of factors affecting licensing practices and alcohol harms.

Intensity of PHT and licensing activity will be assessed by two separate composite ordered categorical measures which will generate an intensity score for PHT activity and for licensing activity within each area in a given period. Firstly, all data will be analysed using NVivo. Then the measures will each be devised in an iterative process of development and testing using analysed data and consultation with UK and international experts.

The first draft of each measure will define dimensions and indicators for different categories of PHT or licensing activity and will be developed based on current research literature and published best practice guidance. This draft will be used to code data a subset of interventions areas, and then all intervention areas, revising as needed at each stage. The resulting measure will be sent to UK-based public health and licensing experts, to review for clarity, completeness and relevance and then further revised based on their feedback. The range of practice for each included indicator of intensity will be analysed by each researcher, and discussed and combined to develop a single measure and defined grading scales for each included indicator. This version will then be applied independently by two researchers to a subset of intervention and control area data, and the resulting scores compared in discussion, checking for consistency and face validity. The final stage of development will involve deciding, using our data, and in consultation with experts, whether and how different dimensions or indicators within the measure should be weighted. Weightings will also be informed by parallel work by the team to further develop a theory of change for PHT involvement in licensing.

Once the measures have been finalised using this iterative process, they will be reapplied to the data for all intervention and control areas to calculate intensity scores for each 6 month period April 2012 to March 2019. Two researchers will apply the measure to 10% of areas (*n* = 4) to examine inter-rater reliability. Where identified, discrepancies will be discussed and assessed by a third reviewer as needed. The scoring system will then be revised and another 4 areas assessed by two reviewers. In the event of further serious discrepancies, this process will be repeated. We will report the inter-rater reliability of the finalised measure.

The agreed intensity scores will be used to examine the relationship between intervention intensity, licensing regime activity and alcohol-harm outcomes.

The final element of primary data collection will involve in-depth qualitative interviews with public health practitioners and other stakeholders in each intervention areas (up to 80 in total). These other stakeholders may include: local authority licensing practitioners, police, trading standards officers, licensing board members and others. These interviews will focus on alternative perspectives on public health involvement in licensing. Semi-structured topic guides will be developed in consultation with our practitioner representative and advisory group in line with our research questions, informed by relevant literature. All interviews will be audio-recorded. Audio-recordings will be transcribed verbatim by experienced transcribers, transcripts checked for accuracy, and anonymised. Detailed field notes will supplement interviews conducted during site visits to intervention areas and will inform later analysis. Analysis will use a collaborative, qualitative framework approach [75, 76] to identify the themes arising and to compare between England and Scotland, different stakeholders and PHTs.

### Analysis of primary outcomes

We will evaluate temporal trends in all key outcomes from 2009 to 2018 and compare these in intervention and control areas using hierarchical log-rate growth models. This method was previously used by members of the research team to investigate the association between a metric of ‘licensing activity’ and alcohol related hospital admissions [28, 30] and crime rates [29] in England.

An additional feature of this study over and above those studies, is the chunking of the intervention intensity measure into 6-month intervals enabling specific exploration of causal effects through inclusion of pre/post indicators and interactions in the growth models as well as the use of ‘Differences-in-Differences’ statistical methods [77]. Inferences about causality can be made through quantitatively evaluating, using a pre-specified plan based on the emergent theory of change, whether there is statistical evidence of changes in longitudinal trends in outcome measures that coincide with the expected effect of the intervention (and is not present in the corresponding control area). Where data is available we will analyse outcomes by deprivation and gender.

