1. INTERVENTION SCOPING & PROCESS EVALUATION: To describe and explore PUBLIC HEALTH TEAM (PHT) engagement in alcohol premises licensing, the local licensing regime and related processes in 20 high activity and 20 low activity PHTs over the period 2012–2018. a. Identify and recruit 40 local PHTs in England and Scotland that vary demographically and in the timing, breadth, components and intensity of their efforts to engage in alcohol premises licensing since 2012. b. Establish a clear picture of PHT, licensing and confounding activity in each area from 2012 to 2018. c. Establish measurable indicators of the intensity and costs of PHT engagement in licensing and local licensing activity in each area. d. Explore perceived mechanisms of change and real and perceived barriers to PHT engagement in licensing, from the perspectives of public health, licensing, police and other stakeholders.	
2 ALCOHOL HARMS EVALUATION: To quantitatively evaluate whether PHT engagement in licensing has a measureable impact on health harms and crime rates using routine data from 2009 to 2018. a. Match the selected intervention local areas to 20 best possible control areas using genetic matching. b. Collect quantitative data on a set of key alcohol harm and crime outcome indicators on which subsequent evaluation will be based. c. Evaluate if, and to what extent, the intensity and components of the intervention are associated with subsequent measureable changes in the key outcome indicators.	
3. WIDER IMPACTS, COSTS AND DISTRIBUTION OF EFFECTS: To examine implementation costs, estimate the short-term impact of PHT engagement in licensing on alcohol consumption and the longer-term impact (up to 20 years) of the intervention on health and healthcare costs and explore the likely distribution of effects across the population. a. Estimate and compare the overall costs to PHTs of implementation activity b. Develop locally-specific policy models for each active intervention area. c. Use these models to estimate the wider impacts of the intervention in terms of long-term health benefits, NHS cost savings and how these impacts may affect health inequalities d. Estimate the potential impact of high intensity PHT activity in two exemplar areas (one in England, one in Scotland) which are not currently active.	

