### Impact

Prior to the study’s commencement we developed a simple linear theory of change to guide our evaluation design. This can be seen in Fig. 1, in which different aspects of local PHT activity are theorised to contribute to changes to local alcohol licensing regimes, which in turn impacts on health and crimes outcome. Figure 2 adds some confounding factors to the theory. Using data collected during work package 1 we will revise and expand on this simple theory of change, producing a fuller list of activities, confounders and incorporating a systems lens.

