**Fig. 2 Fig2:**
[figure not shown]
Simplified theory of change with major confounding variables and activity added

In developing the revised theory we will consider multiple mechanisms of action, some of which may be complementary and some competing, as well as feedback loops and adaptations in the licensing system resulting from different approaches to public health involvement. For example, some actions may focus on indirect mechanisms of action (influencing the nature and type of applications accepted e.g. licensed arts venues but not nightclubs [49]) whilst others may focus more directly on reducing the number of new licences granted through stronger licensing policy.

The emergent theory of change will be informed by practitioners’ views expressed in interviews, and detailed information on local licensing policy and decisions gathered via documentation analysis from WP 1 as well as outcome data from WP 2. The final theory (or theories) will be developed by the full study team, in consultation with the study advisory group and practitioners via a ‘stakeholder workshop’. We will invite all participating areas to attend this workshop at which we will present emerging findings and the draft theory of change.

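### The causal analysis plan is called pre-specified, yet the emergent theory of change it rests on is said to draw on the WP2 outcome data that the plan will test

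*Protocol article*

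**What the plan says.** Four places in the protocol article bear on this.

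- **Analysis of primary outcomes.** Causality is to be inferred by testing, "using a pre-specified plan based on the emergent theory of change", whether outcome trends change when the intervention would be expected to act, with no such change in the matched control area.
- **Impact, text after Fig. 2.** "The emergent theory of change will be informed by practitioners’ views expressed in interviews", together with local licensing information "gathered via documentation analysis from WP 1 as well as outcome data from WP 2". The next sentence moves on to the final theory.
- **Impact, opening paragraph.** This gives a narrower source: "Using data collected during work package 1 we will revise and expand on this simple theory of change".
- **Data collection.** The last step in building the intensity measure is "deciding, using our data, and in consultation with experts, whether and how different dimensions or indicators within the measure should be weighted". It continues: "Weightings will also be informed by parallel work by the team to further develop a theory of change for PHT involvement in licensing". The scores then serve as the exposure: "The agreed intensity scores will be used to examine the relationship between intervention intensity, licensing regime activity and alcohol-harm outcomes".

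Table 1 defines the WP2 objective: "To quantitatively evaluate whether PHT engagement in licensing has a measureable impact on health harms and crime rates using routine data from 2009 to 2018". Its outcome data are therefore the data on which the causal plan is tested.

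**The concern.** A plan is pre-specified only if nothing it depends on was learned from the data it will be tested on. Here the plan depends on a theory, and one of that theory's stated inputs is the outcome data. The theory can reach the test by two routes. It sets the expected effect that trend changes are compared with. It also contributes to the weights of the intensity score, which is the exposure.

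If either is adjusted with knowledge of the harm outcomes, the nominal 5% error rate no longer holds for the analyses that use it. Areas are not randomised and the outcomes are routine series from 2009 to 2018. Fixing hypotheses and exposure definitions in advance is therefore one of the main protections for any causal statement from these analyses.

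**Working it through.** No figure in the protocol is disputed. The check is a reading of the text, followed by an illustration of scale.

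**Tracing the text**

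1. The causal plan is based on the emergent theory (Analysis of primary outcomes).
2. The emergent theory is informed by WP2 outcome data (Impact, after Fig. 2). The same term is used in both places, and the WP2 input is attached to it before the text turns to the final theory.
3. WP2 outcomes are what the plan tests (Table 1, objective 2).
4. From 1 to 3, taken literally, the tested outcomes can inform the expected effects.
5. The weights are also informed by parallel theory work (Data collection). This link is weaker. Theory is one input beside study data and experts, and the article does not say that harm outcomes are used to choose weights.
6. The opening of Impact names only WP1 data for the revision. That disagrees with step 2 and does not cancel it.
7. Lags are to be specified before analysis, from literature and the advisory group (Outcomes of interest). That covers lags but not the weights, the components or the rest of the expected effect.
8. The article states no point at which theory, plan or weights are frozen relative to WP2 outcomes.

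**Scale, under assumptions that are not in the documents**

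(a) Choosing the best of k independent specifications after seeing the outcomes, each tested two-sided at 5%, gives a false-positive rate of 1 − 0.95^k:

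- k = 2: 1 − 0.9025 = 9.8%
- k = 3: 1 − 0.8574 = 14.3%
- k = 5: 1 − 0.7738 = 22.6%
- k = 10: 1 − 0.5987 = 40.1%

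(b) Null simulation. The protocol supplies 40 areas (20 + 20), 5% two-sided, and eight intervention components (Table 5, a to h). The pairwise correlation between components, and one simple correlation test per area-level score, are assumptions. There were 5,000 runs per setting.

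| Components | Correlation | Equal weights fixed in advance | Best-fitting component chosen |
|---|---|---|---|
| 3 | 0.3 | 5.3% | 13.3% |
| 3 | 0.6 | 4.5% | 11.6% |
| 5 | 0.3 | 4.8% | 20.2% |
| 5 | 0.6 | 5.4% | 16.6% |
| 8 | 0.3 | 5.4% | 29.9% |
| 8 | 0.6 | 4.6% | 23.1% |

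Over correlations of 0 to 0.8, the best-of-eight rate runs from about 34% down to about 16%.

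(c) Weighting all eight components by their outcome correlation (correlation between components 0.5) gives about 44%, but this allows negative weights. If weights must be non-negative and favour harm reduction, false protective findings are about 42%, 18%, 8% and 3% at correlations 0, 0.3, 0.5 and 0.8, against 2.5% nominal. With highly correlated components, little inflation remains under that restriction.

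**The case against.** The best defence is that two versions of the theory are meant. A WP1-based revision would drive the analysis plan, and WP2 results would feed only the WP4 synthesis. The opening of Impact supports this, as does the Overview, where WP4 combines findings from all work packages into a theory of change. It is a plausible account of what the authors intend. It does not settle the matter, because the sentence that names WP2 outcome data attaches them to the emergent theory, which is the term used for the basis of the causal plan.

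Three further objections stand and limit the point.

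- In context, the study data used for weighting most naturally mean the coded activity timelines. Weights fitted to harm outcomes are described nowhere.
- The comparison of trends between intervention and control areas uses neither the theory nor the weights. Intervention areas are chosen from expert advice, published reports, prior research and scoping calls. Controls are matched on 2009–2011 covariates.
- The simulated rates model full tuning to the outcomes in a simple test. The article describes expert- and theory-informed weighting followed by hierarchical growth models.

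It could also be said that lock dates belong in an analysis plan that is not shown. Their absence alone would be no finding. But the article itself claims pre-specification and then describes an input that contradicts it, and an analysis plan based on that theory would inherit the conflict.

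**Conclusion.** The point holds as a contradiction in the text. Taken literally, a plan based on a theory informed by WP2 outcomes is not pre-specified for a test on those outcomes. It affects the theory-based causal analyses and, less directly, the intensity-score analyses.

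The size of any inflation is unknown, because it depends on how far WP2 data shape the theory and weights. The rates above are extreme illustrations that rest on assumed correlations and a simplified test. They are not forecasts for this study.

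A reader might infer that the study's test is circular as an established fact, that the theory fixes the weights, or that the primary high-versus-low comparison is compromised. The documents support none of these. The feedback is permitted by the wording but not described as a procedure. The theory is only one input to the weights. The trend comparison does not clearly depend on either, and the lags are already to be set beforehand.

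**What to change.** Reconcile Data collection, Analysis of primary outcomes and both paragraphs of Impact by distinguishing two versions of the theory.

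- **Version for the analysis plan and intensity weights.** It uses only WP1 material, literature and expert input. It is dated and locked before WP2 outcome data are linked to areas or intensity scores.
- **Later version, the WP4 product.** It may use WP2 outcomes. It is not fed back into the confirmatory models, and any analysis it prompts is labelled exploratory.

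The existing commitment on lags can stay as it is. The cost is some wording and a dated lock, with no new data. The drawback is that insights gained after the lock cannot change the confirmatory analysis.

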### Cost-effectiveness analysis and modelled impacts

Within the primary data collection, estimates of staff time and resource use involved in PHT intervention activities will be obtained for each intervention area. We will use this data to estimate the cost of PHT engagement in licensing, both overall and in terms of individual components of activity.

The Sheffield Alcohol Policy Model (SAPM) is an advanced epidemiological simulation model which has previously been used to estimate the impacts on alcohol consumption and related harms of a wide range of alcohol policies, including those affecting price, outlet density and licensing hours in both England and Scotland at the national level [58, 78, 79]. Previous versions of SAPM have been developed at national level. Within this study we will develop new, Local Authority-level models for each intervention area using local data on alcohol consumption, demography and alcohol-related harms.

Using these local versions of SAPM, we will produce estimates of the changes in alcohol consumption, alcohol-related harm and associated healthcare costs, and the distribution of these changes across the local population, resulting from the implementation of local policies and interventions. We will also create models for 2 exemplar control areas, selected from the control areas, based on data availability and the extent to which the PHT is interested in increasing the intensity of their activity. These models will produce estimates of the potential impacts of increasing PHT activity on health and crime outcomes in these areas.

As described above, PHT engagement in licensing is intended to affect the local alcohol licensing system, and therefore (assuming licensing policy directly affects alcohol consumption and drinking behaviour) to impact on key outcomes measured in the general public including health and crime. However, alcohol consumption and harms are not evenly distributed across the population, and intervention activity may impact differently on different population groups. Considering this variation is key to understanding both the true impact of an intervention and also the potential for the intervention to alter these distributions and narrow or widen existing socioeconomic and gender inequalities in health [80–82]. SAPM addresses this by modelling baseline consumption and harm, policy effects, and all outcomes fully stratified by deprivation as well as age, gender and drinking level.

The study will explore these issues and the potential for licensing engagement and policy to affect these socioeconomic gradients through: a) using the Local Authority versions of SAPM and b) exploring the differential impact of the intervention on health outcomes by gender and socioeconomic group (defined by quintiles of the relevant Index of Multiple Deprivation or other relevant markers) to establish the potential of intervention activity to reduce (or exacerbate) the substantial existing inequalities in alcohol-related harms [12].

